### Recruitment

2.9

Patients are recruited by physician investigators, who daily screen stroke admissions and contact attending vascular neurologist as needed to ensure patient recruitment before discharge. The neurology staff is reminded about the study during the year with a short presentation during regular clinical meetings. The recruitment objective was 6 patients per month, but the rate has been 4 per month. We expect complete recruitment by the end of 2022.

### Measurements

2.10

Anthropometric measurements are performed by a study nurse or a study nutritionist according to the study schedule (Table 1). Weight and height are measured by using standard calibrated scales, respectively; waist circumference midway between the lowest rib and the iliac crest by using an anthropometric tape, and blood pressure after 10 minutes of rest in triplicate with a standard calibrated sphygmomanometer.

Blood samples are collected following overnight fasting for at least 10 ± 2 hours, at baseline and at 3 months, coded, centrifuged, and processed in the morning (lipids) at Clínica Alemana or stored at <80°C until assayed (for inflammatory biomarkers, see supplement) at The Medical Chemistry Center, Universidad del Desarrollo. Total cholesterol, LDL-C, HDL-C, and TG are processed with a homogeneous enzymatic colorimetric test in the chemistry automatic analyzer COBAS 8000 platform (Cobas, Roche Diagnostics) upon arrival to the laboratory. All tests are performed according to the manufacturer's instructions. The laboratory technicians are masked to the interventions. Analyses are performed for each participant in frozen samples of whole serum or plasma, as appropriate. Details of the analysis are provided in the Supplementary Material.

### Data collection, retention, and follow-up

2.11

Data collection and follow-up assessments are performed by trained study personnel according to the schedule in the table. Patients are encouraged to stay in the study even if they are non-adherent to the assigned intervention diet and complete follow-up assessment. Extra telephone calls are performed by the study nutritionist according to the patient's needs.

### Feasibility, adherence, and acceptability

2.12

To maintain adherence to and assess the feasibility of the intervention, participants are contacted by telephone at 1 and 2 months after recruitment. The telephone calls are made by study nutritionists to each participant to reinforce the allocated diet and administer a 24-hour diet recall questionnaire. Patients have extra telephone calls and email contacts depending on the individual evaluation of each nutritionist.

To increase adherence, randomized patients are transferred monthly an amount of money equivalent to buying avocado (2 kg per week, including family consumption) or whole grain bread (2 kg per week, including family consumption), according to the allocated diet.

The acceptability of the trial in both groups is assessed with a structured 14-item self-applied (or caregiver) questionnaire performed at the end of follow-up. Items are measured using a 5-point Likert scale.

### Safety

2.13

Adverse events associated with the intervention diet are collected from the time of consent until the final 3-month follow-up visit for each participant, whether considered related to the intervention study or not. All adverse events are followed up until they are resolved and are adjudicated by an independent investigator. Investigators assess any adverse effects of the interventions by administering a checklist of symptoms, including mouth symptoms, bloating, fullness, indigestion, altered bowel habits, other diet-related symptoms, and any other symptoms. Serious adverse events are defined according to International Good Clinical Practice recommendations.^[32]^ Safety specifically include all cardiovascular events (acute myocardial infarction, any stroke, cardiovascular procedures, and cardiovascular deaths) and deaths. All patients are adjudicated by an independent investigator and handled by the treating physician.

### Data quality assurance

2.14

The trial data quality is monitored by the study team. Data access is restricted to trained staff with unique password-protected accounts. No interim analyses will be performed. Independent yearly audits are performed by the Institutional Review Board and approved by the ethics committee.

### Data management

2.15

Data is collected in paper case report forms and transferred to a Research Electronic Data Capture institutional database (REDCap Vanderbilt University) by the study personnel. Identifiable data is not recorded in the database or other documents, and participants are identified busing a unique trial ID. Documents are kept securely in a locked filing cabinet in an office, together with the signed informed consent forms that are accessible only to key research team members. Only the steering committee members and the study statistician will have access to the final trial datasets. Participant files and other source data (including copies of protocols, questionnaires, original reports of test results, correspondence, and records of informed consent) will be kept for 5 years after completion of the study.

### Sample size estimates

2.16

The sample size was calculated using data from previous small, randomized trials of Avocado-based diets on LDL cholesterol in primary prevention, showing a mean of 131.2 (9.4) mg/dL in the standard diet group and 126.6 mg/dL (4.6) in the Avocado-diet group.^[33]^ A sample size of 100 patients per group (200 in total) was estimated to provide 80% power and 5% level of significance with 10% loss and 5% crossover to detect the same difference in LDL-C after 3 months of intervention in patients with IS.

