**Patients and methods::**

Prospective, randomized open-label, blinded outcome assessment clinical trial. Participants are patients within a month of being admitted with an ischemic stroke, who consent and fulfil the eligibility criteria. Patients are randomly assigned to either diet intervention in a 1:1 ratio on top of the usual secondary prevention treatment. The intervention diet is:

The main efficacy outcome is a reduction in plasma LDL-C levels at 3 months of the dietary intervention. Secondary outcomes include changes in the levels of serum lipid profile and serum inflammation markers, safety, and feasibility. A sample size of 200 patients was estimated to provide 80% power and 5% level of significance (10% loss and 5% crossover) to detect a minimum difference of 4.6 mg/dL in LDL-C after 3 months of intervention.

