### Trial design

2.1

Prospective, randomized, open-label, blinded outcome assessment (PROBE design), investigator-driven, controlled superiority clinical trial.

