To maintain diet fidelity with the intervention, in all contacts the study nutritionist emphasizes that the portions and frequencies of food of the diet assigned to the patient are respected, solve specific doubts, and inquire about AE and SAE. The food surveys are analyzed qualitatively and quantitatively by the study nutritionist in charge of carrying them out. The qualitative analysis considers the number of meals per day, fluid intake, and quality of the food consumed, which is compared to each of the diet interventions. The quantitative analysis is carried out by obtaining the ingredients and quantities of each food preparation that the patient consumes, this is then transformed into portions to obtain the intake of calories, carbohydrates, fats, and proteins. This is compared with the requirements of the assigned diet and the % of adequacy is calculated ([intake value/requirement value] × 100). An adequate intake is considered if the macronutrient is in a percentage of adequacy of 90% to 110%. We use as a reference the contributions of nutrients and calories from the “Exchange portions and Chemical Composition of foods of the Chilean food pyramid” National Institute of Food Technologies, 1999 and its update “Food Composition Table” National Institute of Food Technologies, 2018.^[31]^ This information is used to personalize each interview and adjust counselling.

As part of the institutional protocol and Chilean stroke national guidelines, all patients receive appropriate secondary stroke prevention and are discharged with an antithrombotic statin at high doses (usually atorvastatin 80 mg day, a hypotensive, and if necessary, a hypoglycemic drug). The patients are counseled at each study visit to keep their secondary prevention medications according to their treating physician prescriptions.

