#### Primary outcome

2.8.1

The main efficacy outcome is a reduction in the mean level of plasma LDL-C at 3 months of 4.6 mg/dL (0.3 mmol/L) or more in the intervention diet group compared to the control diet group.

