The alpha error level was set to 0.05. Data will be processed in STATA (Stata version 16.0, StataCorp).

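### The stated 200 patients for 80% power do not follow from the printed means and bracketed values, which give 96–98% or 84–87% power depending on how they are read; the true power is unknown

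*Protocol article*

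**What the plan says.** Section 2.16 (Sample size estimates) takes its inputs from small randomised primary-prevention trials of avocado diets: "showing a mean of 131.2 (9.4) mg/dL in the standard diet group and 126.6 mg/dL (4.6) in the Avocado-diet group". The brackets are not labelled as SDs, standard errors or anything else. The section then concludes: "A sample size of 100 patients per group (200 in total) was estimated to provide 80% power and 5% level of significance". This is meant to allow for losses of 10% and crossover of 5%, and to apply the earlier trials' difference to stroke patients. The abstract repeats the 200 patients and 80% power "to detect a minimum difference of 4.6 mg/dL in LDL-C after 3 months of intervention".

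Other relevant statements:

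- Section 2.17 states "The alpha error level was set to 0.05". It does not say one- or two-sided. Section 2.1 describes a superiority trial.
- Section 2.17 analyses the primary outcome by analysis of covariance, with baseline LDL-C and statin use as covariables. No baseline correlation or residual SD enters Section 2.16.
- Section 2.7 says patients leave hospital on a high-dose statin, "usually atorvastatin 80 mg day". No LDL-C SD is given for such patients.

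**The concern.** The article prints both the inputs and the result of its sample size calculation, so the result can be checked, and it is roughly double what the inputs give when read as SDs. The inputs also look doubtful in themselves. The second bracketed value, 4.6, is exactly 131.2 − 126.6. If both values are SDs, the variance in one diet arm is 9.4²/4.6² = 4.2 times that in the other.

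The 80% figure is a headline property of the trial. The 4.6 mg/dL difference is also written into the primary outcome in Section 2.8.1, and the Discussion says the trial will help design a phase 3 trial. If the power statement has no sound basis, readers cannot tell how much a null result says about a 4.6 mg/dL effect, and an unsound SD could be carried into the next design.

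**Working it through.** **Inputs.** From Section 2.16: difference 131.2 − 126.6 = 4.6 mg/dL; bracketed values 9.4 and 4.6; power 80%; significance 5%; loss 10%; crossover 5%; 100 per group. Allocation is 1:1 (Section 2.5). Two-sided testing is assumed, so (1.960 + 0.842)² = 7.849.

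**Step 1: try to reproduce 100 per group.** n per arm = 7.849 × (SD₁² + SD₂²) / 4.6².

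- SDs 9.4 and 4.6: 7.849 × (88.36 + 21.16) / 21.16 = 40.6, so 41 (42 with a Welch t test).
- SD 9.4 in both arms: 7.849 × 176.72 / 21.16 = 65.6, so 66 (67 with a t test).

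The article does not say how loss and crossover were applied, so several conventions were tried (n per arm, normal approximation, before rounding up):

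| Divisor | SDs 9.4 / 4.6 | SD 9.4 in both |
|---|---|---|
| 0.9 × 0.95 | 47.5 | 76.7 |
| 0.85 | 47.8 | 77.1 |
| 0.9 × 0.95² | 50.0 | 80.7 |
| 0.9 × 0.90² (5% crossover in each arm) | 55.7 | 89.9 |
| 0.85² | 56.2 | 90.7 |

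The t-test sizes with the last divisor give the upper ends: 42/0.7225, rounded up to 59, and 67/0.7225, rounded up to 93. The totals are therefore about 96 to 118 for 9.4/4.6 and about 153 to 186 for 9.4 in both arms. One-sided testing with 9.4/4.6 moves further away, to about 76 to 90 in total. None of these reaches 200.

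**Step 2: power with 200 randomised.** Ten per cent loss leaves 90 evaluable per arm. Crossover dilutes the effect to 4.6 × 0.95 = 4.37 (one arm) or 4.6 × 0.90 = 4.14 (each arm).

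- SDs 9.4/4.6: standard error √(109.52/90) = 1.103. Power is about 97.6% at 4.37 and 96.1% at 4.14.
- SD 9.4 in both arms: standard error √(176.72/90) = 1.401. Power is about 87% at 4.37 and 84% at 4.14.

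**Step 3: which SD would give 80%?** Common SD = effect / [2.802 × √(2/90)]. This is 11.0 for the undiluted 4.6, 10.5 for 4.37 and 9.9 for 4.14. No such SD appears in the article.

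**Step 4: range for an unknown residual SD.** The SDs below are assumptions; none is in the documents. All rows use 90 per arm and the diluted effect. The detectable difference is 2.802 × SD × √(2/90), divided by 0.95 or 0.90 so that it is on the same diluted basis.

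| Assumed residual SD | Power for 4.6 mg/dL | Difference detectable with 80% power |
|---|---|---|
| 10 | 79–83% | 4.4–4.6 mg/dL |
| 12 | 63–68% | 5.3–5.6 mg/dL |
| 15 | 45–49% | 6.6–7.0 mg/dL |
| 20 | 28–31% | 8.8–9.3 mg/dL |

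**The case against.** **The reading of the brackets is uncertain.** If 4.6 is a misprinted difference and 9.4 is the SD for both arms, 100 per group is conservative by only about 10 to 20%. This stands: the factor of two applies to one reading only. It does not rescue the claim, because the second reading gives 84–87% power and not 80%.

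**The article condenses a fuller protocol.** Formula, sidedness and crossover convention may be set out there. That is fair, and their absence is not the complaint. The complaint is that the printed inputs and the printed result disagree under every standard convention tried.

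**Under-power is not shown.** A reader might infer that the trial is too small, because inputs from small primary-prevention studies are applied to stroke patients on high-dose statins. The documents do not support that conclusion. On the printed inputs the trial is over-powered. The article gives no SD for its own population, and similar high-dose statin treatment could narrow the spread of LDL-C as well as lower its mean. Covariance adjustment also reduces the residual SD: a raw SD of 15 with an assumed baseline correlation of 0.8 leaves 15 × √(1 − 0.64) = 9.0. The mean level of 131 does not enter the power formula at all.

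**The practical effect is small.** N is fixed, and the test, alpha and primary analysis are unaffected. This stands, and it is why the remedy is limited to correcting the statement.

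**Conclusion.** The concern holds as an inconsistency between printed inputs and printed result. Under two-sided 5% testing, 200 patients give about 96–98% power if the brackets are SDs of 9.4 and 4.6, and about 84–87% if 9.4 applies to both arms. The stated 80% requires a common SD of about 9.9 to 11.0 that the article does not give. That 4.6 is not an SD is a reasonable suspicion, because it equals the mean difference, but it is not established.

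The direction of the real error is unknown. Power falls below 80% only if the residual SD after covariance adjustment exceeds about 10 to 11, and the documents give neither that SD nor a baseline correlation. The figures for SDs of 10 to 20 show how much depends on the missing value; they do not predict this trial's power.

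**What to change.** Keep N = 200. In Section 2.16 and the abstract:

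1. Say what the bracketed values are, and give the SD actually used.
2. Correct the calculation so that SD, power and N agree.
3. Restate power and detectable difference for 200 patients, using a blinded pooled residual SD of 3-month LDL-C from patients already followed, or over a stated range of SDs. No arm is revealed or compared, so this is compatible with the no-interim-analysis statement in Section 2.14. Pooling over arms adds at most 4.6²/4 = 5.3 to the variance if the true effect is 4.6, for example 10.3 in place of 10.
4. Drop the 80% claim if it does not hold.
5. State that a null result will be interpreted from the confidence interval for the LDL-C difference.

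The cost is a wording change and one blinded SD calculation. Recruitment, treatment and the primary analysis are unchanged. The drawback is that the stated power may become less favourable.

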### Statistical analyses

2.17

All efficacy analyses will be performed according to the intention-to-treat principle. The primary outcome will be compared between the 2 groups by an analysis of covariance adjusting for baseline measures unbalanced by randomization and with baseline LDL-C and statin use (initial and final doses) as covariables. To account for missing data, multiple imputations using chained equations will be used, assuming randomness. The results will be compared to those with complete data. A sensitivity analysis will be carried out to investigate the robustness of the findings according to adherence to the intervention. Safety analysis will be performed for all patients participating in the study. The number of patients with AEs, the occurrence of specific SAEs, and discontinuation due to SAEs will be tabulated. Binary outcomes, such as AEs, major cardiovascular events (acute myocardial infarction, stroke, or vascular death), or death will be analyzed with the Chi-2 test for independence. Analysis of adherence will be performed in all patients who finalized the study. The proportion of patients who completed the intervention at 3 months will be analyzed using the Chi-2 test for independence. The percentage of adequacy of the diet intervention at 1, 2, and 3 months will be analyzed with generalized linear mixed models for repeated measures. Feasibility assessed as the mean time from symptom onset to intervention will be analyzed using Student's *t* test. Analysis of the acceptability 14-item questionnaire will be performed in all patients completing the follow-up with the Mann–Whitney–Wilcoxon non-parametric test. Exploratory subgroup analyses will be carried out irrespective of whether there is a significant treatment effect on the primary outcome. These analyses will be adjusted for confounders. The following pre-specified subgroup analyses will be performed by adding an interaction term to the models: age (< or ≥ mean) years, sex, education level < or ≥12 years, post-stroke disability (modified Rankin score < or ≥1), physical activity (Rapid Assessment of Physical Activity questionnaire score < or ≥6), MEDAS score (< or ≥ median), dyslipidemia (yes/no), diabetes/insulin resistance (yes/no), BMI (< or ≥25), and BMI (< or ≥30). Per protocol analysis will be performed for the primary and key secondary efficacy outcomes, using the same statistical test as per the intention-to-treat analysis.

The alpha error level was set to 0.05. Data will be processed in STATA (Stata version 16.0, StataCorp).

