### Randomization

2.5

Eligible patients are randomly assigned in a 1:1 ratio by study personnel to either diet intervention, using a desktop minimization program (MinimPy 0.3, Python Software Foundation), balanced by sex, age group <70 and ≥70 years (this is the median age of patients admitted with stroke in Clínica Alemana), and previous adherence to a Mediterranean diet as defined according to the Mediterranean Diet Adherence Screener (MEDAS) score <7 or ≥7 (this is the median score found in stroke patients in our institutional registry) (Fig. 1).^[29,30]^

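### The primary ANCOVA chooses covariates by undefined observed imbalance, so the model is not fixed in advance and tends to omit the minimisation factors

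*Protocol article*

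**What the plan says.** In the protocol article, section 2.17 (Statistical analyses), the primary outcome is compared by "analysis of covariance adjusting for baseline measures unbalanced by randomization", and the same sentence adds baseline LDL-C and initial and final statin dose as covariates. It gives no list of candidate measures and no criterion for imbalance. None of the minimisation factors is named.

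Section 2.5 (Randomization) describes 1:1 allocation by minimisation, "balanced by sex, age group <70 and ≥70 years", and on prior diet by "Mediterranean Diet Adherence Screener (MEDAS) score <7 or ≥7". It explains that 70 is the institution's median age for stroke admissions and 7 the median MEDAS score in its registry.

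Further on, section 2.17 lists exploratory subgroups, among them "age (< or ≥ mean) years", sex, and "MEDAS score (< or ≥ median". Section 2.6 (Masking) says that data analysts do not know the diet allocation.

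**The concern.** There are two linked problems.

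First, a covariate rule that depends on observed imbalance leaves the primary model open until the data are in. Imbalance could mean a p-value below 0.05 or 0.10, or a standardised difference above 0.1 or 0.2, and each can give a different model. Imbalance is also a poor guide to which covariates matter. A strongly prognostic variable that happens to be balanced is left out, and an irrelevant one that happens to be unbalanced is put in.

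Second, the rule works against the design. Minimisation makes the arms alike on sex, age group and MEDAS group, so these are the variables least likely to be flagged. If they predict the outcome and are left out, the treatment estimate gains precision from the balance, but the model counts the variation they explain as noise. The reported standard error is then too large. At stake are the pre-specification of the primary result and some efficiency.

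**Working it through.** **The plan's own figure.** Section 2.16 says: "A sample size of 100 patients per group (200 in total) was estimated to provide 80% power", with 5% significance, and "with 10% loss and 5% crossover to detect the same difference in LDL-C". The inputs are means of 131.2 (9.4) and 126.6 (4.6) mg/dL, a difference of 4.6. I take the bracketed figures as SDs and the test as two-sided, since section 2.17 says only that "The alpha error level was set to 0.05". Then (1.960 + 0.842)² = 7.849, and per group:

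- unequal SDs: (9.4² + 4.6²) × 7.849 / 4.6² = 109.52 × 7.849 / 21.16 = 40.6, so 41;
- SD 9.4 in both arms: 2 × 88.36 × 7.849 / 21.16 = 65.6, so 66.

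Under several ways of allowing for loss and crossover, these become 48-57 and 76-91. The stated 100 is not reproduced and is larger than its own inputs require. That is a separate matter. It is relevant here only because it bears on how much the loss of power matters.

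**Expected size of the standard error excess.** Let R2 be the share of outcome variance, given baseline LDL-C, that the three minimisation factors explain. With near-perfect balance, the true variance of the treatment estimate excludes that share, while the residual variance of a model without the factors includes it. So

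model SE / true SE ≈ 1 / √(1 − R2),

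which gives 1.01 at R2 = 0.02, 1.03 at 0.05, 1.05 at 0.10 and 1.12 at 0.20.

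**Simulation.** The document does not give R2, so it was varied. Assumptions: 200 patients; 3,000 trials per setting; biased-coin minimisation (probability 0.9) on three binary factors with 50% prevalence; baseline LDL-C always in the model; statin dose not simulated; eight other baseline variables jointly explaining 10% of residual variance; imbalance taken as p < 0.05 among those eight variables. The effect was set so that the model with baseline LDL-C alone has about 80% power when R2 = 0.

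| R2 | Model SE / true SE, imbalance rule | Type I error, imbalance rule | Power, imbalance rule | Power, factors in model | Gain (points) |
|---|---|---|---|---|---|
| 0 | 1.00 | 5.1% | 80.4% | 80.5% | 0.1 |
| 0.02 | 1.01 | 4.8% | 80.7% | 81.6% | 0.9 |
| 0.05 | 1.03 | 4.2% | 80.4% | 82.3% | 1.9 |
| 0.10 | 1.07 | 3.9% | 80.9% | 84.3% | 3.4 |
| 0.20 | 1.15 | 2.2% | 82.7% | 88.0% | 5.3 |

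The ratios and type I errors are from the runs with no treatment effect. In the runs with an effect, the ratio at R2 = 0.20 was 1.12, so 15% is the upper end. The Monte Carlo standard error of a 5% rejection rate is √(0.05 × 0.95 / 3,000) = 0.4 points, so 5.1% does not differ from 5%. With the three factors in the model, type I error was 4.3-5.3% and the SE ratio 0.99-1.02.

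A separate simulation (180 patients, minimisation probability 0.8, R2 about 0.17) agrees: model SE 0.149 against a true 0.133, a ratio of 1.12; type I error 2.7%; power 82.5% against 87.4% with the factors included.

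**How open the rule is.** In further simulated trials of 180 patients, the four definitions listed under the concern did not all give the same covariate set in 99% of trials. A p < 0.05 rule never selected a minimisation factor in its binary form.

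**The case against.** Four points can be made for the plan.

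*The standard error may be about right.* Baseline LDL-C and statin dose are already in the model and may leave little for sex, age and MEDAS to explain. This stands. A reader might infer that the error bars are simply wrong, but the document gives no R2, and at 0.02 or below the excess is negligible.

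*Analysts are masked.* This lowers the risk of choosing covariates to favour one diet. It does not fix the model, and arms can be compared for imbalance under coded labels. A reader might infer that the rule inflates false positives. One definition applied mechanically did not do so materially. Choosing among the four definitions after seeing the results gave about 5-7% in simulation, but nothing in the document says that this will be done.

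*The minimisation factors are not strictly excluded.* Only the two-way splits are balanced. Age and MEDAS as continuous scores can still differ between arms and be picked up. This stands: the rule tends to omit the factors and does not forbid them.

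*A full covariate list may be in the analysis plan.* A missing list alone would be no finding in a journal article. The article, however, states a rule, and an analysis plan with fixed covariates would have to contradict it.

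Two further inferences fail. It is tempting to say that the trial has little power to spare, but on its own inputs the sample size is generous. It is also tempting to say that the subgroups ignore the minimisation cut-points. Sex matches, the MEDAS median may be the registry value of 7, and only age (mean against 70) visibly differs. Exploratory interaction analyses need not reuse the allocation cut-points.

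**Conclusion.** The concern holds on pre-specification, whatever R2 proves to be: the covariates of the primary model depend on an undefined reading of the data. The effect on precision is conditional. Under the stated simulation assumptions the model standard error is too large by 0-1% for R2 of 0-0.02, 3-7% for 0.05-0.10 and about 15% for 0.20. With a mechanically applied rule, type I error is at or below 5% within simulation error, and the power forgone is about 0-5 points. This is a should-fix point about a badly chosen rule. It does not show that the trial would mislead. The subgroup cut-points are a minor query only.

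**What to change.** In section 2.17, replace the clause on unbalanced baseline measures with a fixed covariate set: those already named, plus sex, age and MEDAS (each of the last two either continuous or at the minimisation cut-point, chosen now). Keep any imbalance-based adjustment as a sensitivity analysis, with its criterion and candidate variables stated. If a separate analysis plan already fixes the covariates, bring the two texts into line. Whether final statin dose belongs in the model is a separate question not argued here.

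The cost is one sentence and about three degrees of freedom. The variables are already collected because allocation uses them. At R2 = 0 the simulated power was unchanged (80.5% against 80.4%), and the planned sample size is not affected.

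In the same edit, state the numeric age cut for the subgroup analysis (the mean, or 70 as in minimisation) and whether the MEDAS median is the registry value of 7.

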### Masking

2.6

Participants and investigators are not masked to the intervention diets; however, outcome assessors of LDL-C and other laboratory results, and data analysts are masked to the diet allocation. Unblinding is not anticipated.

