In the baseline session, the patient receives nutritional counseling and education according to the randomized diet, applying the instruments as described in the study schedule (Table 1). The usual duration of this session is ±90 minutes. At 30 ± 7 and 60 ± 7 days, telephone follow-up is performed by the same nutritionist who inquiries about the diet pattern, applies the instruments according to the study schedule, and provides specific feedback recommendations and reinforcements on the allocated diet pattern. The usual duration of these sessions is ±30 minutes. At 90 + 14 days, follow-up a closing nutritional session is conducted including the application of the appropriate instruments according to the study schedule (Table 1), and the delivery of dietary recommendations for healthy habits as post-trial care. In this session, 1 of the physician investigators obtains the modified Rankin Score, the details of the medications being taken by the patient and details about any AE or SAE if they occurred. The usual duration of this session in ±45 minutes. Before the pandemic, the baseline and 3 months sessions were carried out in person, scheduling a visit to the hospital by the patient, since March 2020 to date these sessions are mixed: measurements and samples in person and intervention/instruments by video conference. If the patient is unable to answer, the caregiver living with the patient or who oversees cooking and feeding the patient is interviewed.

The diets are standard normocaloric adjusted depending on the nutritional status and physical activity of the patient, but the focus of both diets is on the quality of the food and not the quantity. We anticipate that weight loss may occur in some patients due to improved eating habits and food selection. For each intervention, 3 different daily caloric dietary contributions were made: 1500, 1800, and 2000 calories. The macronutrient distribution of each diet intervention is as follow:

A.Mediterranean diet: 50% total caloric value of carbohydrates, 35% fat (22% MUFA fat, 6% polyunsaturated fatty acids (PUFA) fat, ±10% saturated fat), and 15% protein.B.Low-fat high-quality carbohydrate: 55% carbohydrates, 30% fat (12–14% MUFA fat, 6–8% PUFA fat, ±10% saturated fat), and 15% protein.

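### The primary ANCOVA adjusts for the final statin dose, recorded after randomisation, and so can bias the diet effect by an unknown amount in either direction

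*Protocol article*

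**What the plan says.** Section 2.17 (Statistical analyses) opens with "All efficacy analyses will be performed according to the intention-to-treat principle". It then gives one primary model, an analysis of covariance "with baseline LDL-C and statin use (initial and final doses) as covariables". No primary model without the final dose is given, and the model that contains it is not labelled supplementary.

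The rest of the article shows what kind of variable the final dose is:

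- **Timing.** Table 1 schedules the secondary prevention medication questionnaire at baseline and 90 days. Section 2.7 says that at the closing session a physician investigator obtains "the details of the medications being taken by the patient". Table 1 places the outcome blood sample at the same time point.
- **Who sets it.** Patients leave hospital on a high-dose statin, "usually atorvastatin 80 mg day", and are counselled at study visits to "keep their secondary prevention medications according to their treating physician prescriptions". The trial does not hold the dose constant.
- **Masking.** Section 2.6 states "Participants and investigators are not masked to the intervention diets". Laboratory assessors and data analysts are masked.
- **Question asked.** Section 1.1.1 asks about LDL-C at 3 months in patients receiving standard secondary prevention care.

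**The concern.** A covariate fixed before randomisation can only sharpen the comparison between arms. A covariate measured after it can be affected by the diet. Here a plausible chain exists: diet lowers LDL-C, the LDL-C level influences the statin dose, and the dose influences the 3-month LDL-C. Unmeasured causes of a high or low LDL-C can also influence the dose.

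Holding the final dose fixed then does two things. It removes whatever part of the effect of assignment runs through dosing, and it compares patients who share a final dose partly because of their LDL-C. The first departs from the effect of being assigned the diet under usual care. The second prevents the result from being read as the effect of diet with statins held constant. The estimate at stake is the primary one.

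**Working it through.** **Target.** Section 2.16 gives the source data, "showing a mean of 131.2 (9.4) mg/dL in the standard diet group and 126.6 mg/dL (4.6) in the Avocado-diet group". The difference is 131.2 − 126.6 = 4.6 mg/dL, which matches the mg/dL figure in section 2.8.1. Shifts below are judged against it.

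**What adjustment does.** Define

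- τ: direct effect of diet on LDL-C (negative if beneficial);
- β: fall in LDL-C per step up in statin dose;
- Δ: difference in mean final dose, diet arm minus control, given the baseline covariates;
- κ: slope of the unmeasured determinants of LDL-C on final dose, given arm and baseline covariates.

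Then

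- coefficient without final dose (effect of assignment) = τ − βΔ;
- coefficient with final dose = τ − κΔ;
- shift (with minus without) = (β − κ)Δ.

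Three things follow. If final dose does not differ by arm (Δ = 0), there is no shift. If it differs and patients with high LDL-C tend to be on higher doses (κ > 0), the adjusted coefficient misses the direct effect τ as well. With Δ negative (fewer increases on the diet), the shift is towards zero when κ > β and away from zero when κ < β.

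**Simulation 1** (400,000 patients per row). All titration parameters are assumed: τ = −4.6 mg/dL, unmeasured LDL-C determinants with SD 12, outcome noise with SD 8, and the log-odds of a dose increase rising with on-diet LDL-C by the slope shown. The simulation error of a coefficient is about 2 × √(12² + 8²)/√400,000 ≈ 0.05.

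| Slope per mg/dL | β | Δ | Without final dose | With final dose | Shift | Implied κ = β − shift/Δ |
|---|---|---|---|---|---|---|
| 0 | 5 | 0.000 | −4.60 | −4.60 | 0.00 | – |
| 0.04 | 5 | −0.032 | −4.51 | −4.50 | +0.01 | 5.3 |
| 0.04 | 15 | −0.033 | −4.11 | −4.43 | −0.32 | 5.3 |
| 0.08 | 5 | −0.059 | −4.31 | −4.04 | +0.27 | 9.6 |
| 0.08 | 15 | −0.060 | −3.81 | −4.14 | −0.33 | 9.5 |
| 0.15 | 5 | −0.085 | −4.26 | −3.52 | +0.74 | 13.7 |
| 0.15 | 15 | −0.085 | −3.37 | −3.49 | −0.12 | 13.6 |

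The implied κ agrees within each pair of rows, as the formula requires, because κ depends on the titration rule and not on β. For example, in the sixth row −4.26 → −3.52 is a shift of +0.74, and κ = 5 − 0.74/(−0.085) = 13.7. With no true diet effect and dosing driven only by LDL-C, both coefficients were about 0.

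**Simulation 2** (2 million patients; assumed τ = −4.6, β = 6, residual SD 20).

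| Titration | Without final dose | With final dose | Shift |
|---|---|---|---|
| log-odds 0.02 per mg/dL | −4.48 | −4.44 | 0.04 |
| log-odds 0.05 per mg/dL | −4.32 | −3.85 | 0.47 |
| log-odds 0.10 per mg/dL | −4.25 | −3.04 | 1.21 |
| strict LDL-C threshold | −4.08 | −1.95 | 2.13 |

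**Two further patterns**, also on assumed parameters:

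- *Dose reductions instead of increases* (6 mg/dL rise per reduction, strongly tied to low LDL-C): −4.21 without and −3.83 with, a shift of 0.38.
- *Dosing influenced by the arm itself, with a true direct effect of zero*: about −0.4 to −0.7 without and −0.7 to −1.2 with final dose. Here adjustment enlarges an apparent benefit.

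**The case against.** The strongest defence is that separating diet from statins is a sensible aim, and that there may be little dose variation to adjust for. Patients usually start on a high dose, which limits increases. They are counselled to stay on their prescriptions. Table 1 schedules study blood only at baseline and 90 days, so no study LDL-C result is available in between to prompt a change. One may add that intention-to-treat, read narrowly, concerns who is analysed and in which arm, and the model does not breach that.

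Much of this stands as a limit on the likely size. It does not rescue the model. Dose reduction, stopping, switching and routine-care testing all remain possible. If doses do not change, the final dose adds nothing beyond the initial dose; if they change in response to LDL-C or arm, it distorts. The aim of isolating diet is also not met, since the adjusted coefficients in the working miss the assumed direct effect of −4.6 whenever dosing tracks LDL-C. The narrow reading of intention-to-treat does not help either, because the stated objective is the effect of the diet in patients on standard secondary prevention care, and later statin changes are part of that care.

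A reader might infer that prescribers know the allocation. Section 2.6 names participants and investigators; section 2.7 refers separately to the treating physician, whose masking is not described. They may learn the allocation in an open-label trial, but the article does not say so.

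**Conclusion.** The point holds as a defect of the specified primary model: it conditions on a post-randomisation variable that may lie on the path to the outcome. That rests on the text alone.

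The size does not. In the patterns tried, the shift ran from nil to 2.13 mg/dL, which is 2.13/4.6 = 46% of the target; only strict threshold titration gave the largest value. The documents state no titration rule, no LDL-C target and no frequency of dose change, so none of these patterns can be called the expected one.

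Three stronger readings are tempting and are not supported:

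- *That the primary estimate is biased.* It can be; this requires dose changes that respond to LDL-C, tolerance or allocation, which the article does not show.
- *That the bias runs towards no effect.* Several scenarios moved away from zero, and arm-driven dosing enlarged an apparent benefit.
- *That about half the effect would be lost.* That is the extreme of the assumed scenarios.

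The case for changing the model is that it protects the promised estimate at almost no cost, not that a particular bias has been demonstrated.

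**What to change.** In section 2.17, delete the final dose from the primary model, so that it adjusts only for variables fixed before randomisation: baseline LDL-C and the initial statin dose recorded at baseline. State that statin changes after randomisation count as part of usual care and do not alter how a patient's 3-month LDL-C enters the analysis.

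Tabulate final statin dose and change from the initial dose by arm. Since the shift is (β − κ)Δ, this table shows directly whether there is a between-arm difference in dose to worry about. If a model with final dose is kept, label it supplementary and state its assumption: given the baseline covariates, no unmeasured factor drives both final dose and LDL-C.

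The change is one sentence, needs no new data, and should be made before any analysis by arm. The downside is slightly more residual variance from statin changes that are left unadjusted.
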